### Time course of interventions/study protocol

At day 0 (visit 1), informed consent is obtained, demographic data are recorded and spirometry, EIT measurements and capillary blood gas analysis performed to retrieve baseline data. Additionally, potentially fertile female patients are submitted to a pregnancy test.

Visit 2 is performed on the day of surgery. A preoperative MRI of the lungs is performed prior to premedication. Preparation for anesthesia and surgery is done according to standard of care. Anesthesia induction and maintenance is standardized according to the following protocol: all weight-derived calculations are based on ideal body weight defined as 50 or 45.5 (male or female, respectively) + 0.91*(height - 152.4): Anesthesia induction is performed with continuous infusion of 0.5 μg/kg/h remifentanil and a bolus of 1 to 2 mg/kg propofol. Neuromuscular blockade to facilitate endotracheal intubation is achieved by bolus administration of 0.2 mg/kg cisatracurium. Maintenance of anesthesia is monitored by bispectral index (BIS level 40 to 60) and is achieved by continuous infusion of 5 mg/kg/h propofol, 0.2 to 0.3 μg/kg/h remifentanil and 0.09 mg/kg/h cisatracurium. Neuromuscular blockade is checked hourly by muscle relaxometry using the train of four ratio aiming at values of 0 to 1. During induction of anesthesia, an electrolyte solution is administered at a rate of 500 ml/h and reduced thereafter to a maintenance rate of 300 ml/h. Noradrenaline can be infused if necessary to ensure mean arterial blood pressure levels >60 mmHg. After induction and prior to the start of surgery, postinduction measurements are performed and patients are then randomly assigned to mechanical ventilation with CV or VV. EIT measurements and blood plasma samples are obtained postinduction, as well as after surgical wound closure (postclosure) before the end of anesthesia. Arterial blood gases are measured hourly throughout surgery and hemodynamics, as well as spirometric data, are recorded from the monitoring system and the ventilator, respectively. Amounts of infused drugs and fluids, as well as blood loss and urine output, are recorded. Visit 3 takes place on the first postoperative day. Spirometry, lung MRI, EIT, plasma blood sampling and capillary gasometry are performed, and adverse, as well as severe adverse, events (AEs, SAEs) are recorded.

Visit 4 is performed on the third postoperative day. Spirometry, EIT, plasma blood sampling and capillary gasometry are obtained, and AEs and SAEs recorded.

Visit 5 takes place on the fifth postoperative day and includes spirometry, EIT, plasma blood sampling and capillary gasometry. AEs and SAEs will be recorded.

Visit 6 represents the final examination before hospital discharge. Spirometry, EIT, plasma blood sampling and capillary gasometry will be measured, and AEs and SAEs will be recorded.

### Technical aspects

For electrical impedance tomography (EIT), a PulmoVista® 500 (Dräger Medical, Lübeck, Germany) will be used. Files will be acquired over 2 min, with a frame rate of 20 Frames/s. Distribution of ventilation across the ventral-dorsal gradient will be determined from relative changes in electrical impedance as described elsewhere [15]. Briefly, images of the EIT device containing 32 × 32 pixels will be recorded at a rate of 20 frames/s during 2 min for offline analysis. Using a dedicated routine (EITa!), the highest and lowest limits of the area containing changes in the impedance (region of interest (ROI)) will be determined. The ROI will be divided into three zones with equal heights (ventral, central and dorsal) and the relative changes in impedance will be computed.

Magnetic resonance imaging (MRI) will be performed preoperatively and at the first postoperative day. Native MRI sequences using T2 (HASTE: TR/TE = 1000 ms/98 ms; 360 ms per slice) and T1 (VIBE: TR/TE = 5 ms/2 ms; 12 s per volume × 2) will be obtained during inspiratory breath hold. A radiologist blinded to the study groups will manually measure thickness of atelectasis and pleural effusions. Volumetric measurements of aerated and nonaerated lung tissue will be performed using manual segmentation and volumetric measurements using the OsiriX software package.

### Study dropouts

Participation in the trial is voluntary. A subject has the right to withdraw from the study at any time for any reason without any consequences for further medical treatment. Furthermore, both investigators, intraoperative as well as postoperative, have the right to terminate the participation of any subject at any time during the part of the study they are responsible for if the investigator deems it in the participant’s best interest. The reasons and circumstances for study discontinuation will be documented in the Case Report Form (CRF). All data are analyzed based on the intention-to-treat (ITT) principle.

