## Methods/Design

### Objectives and design

PROVAR is an investigator-initiated, single center, randomized controlled, two-arm trial comparing CV and VV in patients receiving mechanical ventilation during general anesthesia for open abdominal surgery.

The study protocol is approved by the institutional review board of the Medical Faculty and the University Hospital Dresden, Germany (EK 174052011) and has been registered at clinicaltrials.gov (NCT01683578). PROVAR is conducted in accordance with the Declaration of Helsinki and the principles of good clinical practice.

PROVAR tests the hypothesis that intraoperative VV is associated with improved pulmonary function and reduced systemic inflammatory response compared to CV in patients planned for open abdominal surgery. Primary endpoint is the FVC on the first postoperative day. Secondary endpoints are plasma concentrations of interleukin (IL)-6, IL-8 and tumor necrosis factor alpha (TNF-α); partial pressure of oxygen in capillary blood (PcO_2_) on the first postoperative day; peak expiratory flow (PEF) on the first postoperative day; forced expiratory volume in the first second (FEV_1_) on the first postoperative day; oxygenation (PaO_2_/F_I_O_2_) during surgery; changes of spatial distribution of ventilation measured by electrical impedance tomography (EIT); amount of atelectasis measured with magnetic resonance imaging (MRI) on the first postoperative day; and occurrence of postoperative pulmonary complications defined by the modified clinical pulmonary infection score (mCPIS) [9]. Figure 1 shows the CONSORT diagram of PROVAR.

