Blinding is achieved by means of a modified triple blind design with the patients and postoperative investigators blinded to the treatment and the intraoperative investigator blinded to the pre- and postoperative measurements.

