2. As part of the clinical routine some patients will receive thoracic epidural anesthesia, whereas others who have contraindications will not; therefore, thoracic epidural anesthesia will be implemented as a covariate in the statistical analysis.

3. Generalizability of the study results is critical since until today there is no commercially available ventilator or anesthesia machine able to perform VV.

4. The anesthesiologist in charge of the intraoperative part of the study cannot be blinded to the ventilator mode; we therefore decided to split personnel for intra- and perioperative analysis in order to have at least the perioperative staff blinded to the ventilator mode.

In conclusion, PROVAR is the first randomized controlled trial aiming at intra- and postoperative effects of VV on lung function. This study may help to define the role of VV during general anesthesia requiring mechanical ventilation.

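### The dropout clause lets an investigator who knows the ventilator mode end participation, not just study ventilation, before the day-1 FVC, so the primary outcome can go missing by arm

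*Protocol article*

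**What the plan says.** **Who may end what.** Under Study dropouts, both investigators "have the right to terminate the participation of any subject at any time during the part of the study they are responsible for", on the condition "if the investigator deems it in the participant’s best interest". The reasons go into the case report form, where the event is called discontinuation of the study. The same section closes with "All data are analyzed based on the intention-to-treat (ITT) principle".

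**Who knows the arm.** The Discussion (limitation 4) states: "The anesthesiologist in charge of the intraoperative part of the study cannot be blinded to the ventilator mode". The blinding paragraph hides something else from that person; it has "the intraoperative investigator blinded to the pre- and postoperative measurements". Patients and postoperative investigators are blinded to treatment.

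**Order of events.** After induction and before surgery, "postinduction measurements are performed and patients are then randomly assigned to mechanical ventilation with CV or VV". Objectives and design states: "Primary endpoint is the FVC on the first postoperative day". The only FVC scheduled before that is the baseline spirometry at visit 1.

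**What happens to gaps.** Statistics analyses all patients in their randomised groups and fills missing data by last observation carried forward. It adds a per-protocol analysis if a considerable number of patients miss study therapy or outcome assessment.

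**The concern.** Stopping a study treatment and leaving a study are different events. A patient whose assigned ventilation is stopped can still blow into a spirometer the next day. A patient whose participation is ended, read literally, has no further study visits. The dropout clause gives investigators only the second option and does not say that outcome collection continues.

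The intraoperative investigator decides with the ventilator mode in view, after allocation and before the endpoint. If the decision is influenced by the mode, or by how the patient is doing on it, day-1 FVC will be missing in a way that depends on both arm and prognosis. Analysing as randomised keeps the patient in the correct arm but does not create the measurement. The stated missing-data rule would then enter a preoperative value as a postoperative outcome. If FVC falls after surgery, that flatters whichever arm loses more patients, and most of all if those lost would have done badly.

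**Working it through.** **1. The plan's own figure.** Inputs from Statistics: standardised effect 1.086, two-sided alpha 0.05, power 0.95, Mann–Whitney test. With the normal-parent asymptotic relative efficiency 3/π = 0.955, the effective size per arm is 25 × 0.955 = 23.87.

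- Noncentrality = 1.086 × √(23.87/2) = 3.75, on about 45.7 degrees of freedom.
- Power = 0.957, so the stated 25 per arm is reproduced.
- With 24 per arm, power is 0.949. The 25 is therefore the minimum, and no allowance for missing outcomes is visible.

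**2. Is the problem power or bias?** If outcomes are simply absent, the same formula gives power 0.949 with two lost from one arm, 0.944 with three and 0.932 with five. The loss of precision is modest, so any serious harm has to come through bias.

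**3. Size of the bias under the stated missing-data rule.** Assumptions, none given in the document:

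- k of 25 patients are lost from one arm and none from the other.
- There is no true effect, and day-1 FVC is standard normal in both arms.
- Preoperative FVC lies D = 1 to 3 SD higher, with correlation r = 0.5 to 0.8 with day-1 FVC. The Background says FVC is reduced after surgery but gives no size, and refers only to the first three hours.

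If the k patients lost are those who would have had the lowest day-1 FVC, with mean m below zero, carrying baseline forward shifts the difference by

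shift = (k/25) × [D + (1 − r) × |m|].

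For 25 normal observations, |m| is about 1.74 for the lowest two and 1.58 for the lowest three.

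- k = 2: from 0.08 × (1 + 0.2 × 1.74) = 0.11 to 0.08 × (3 + 0.5 × 1.74) = 0.31 SD.
- k = 3: from 0.12 × (1 + 0.2 × 1.58) = 0.16 to 0.12 × (3 + 0.5 × 1.58) = 0.45 SD.

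If losses are random, the shift is (k/25) × D: 0.08 to 0.24 SD for k = 2 and 0.12 to 0.36 SD for k = 3.

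**4. Two-sided type I error (nominal 0.05), Mann–Whitney, by simulation.**

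| Lost from one arm | Worst performers lost | Random loss |
|---|---|---|
| 2 | about 0.07–0.13 | about 0.05–0.06 |
| 3 | about 0.10–0.23 | about 0.06–0.08 |

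A repeat with 20,000 runs per setting agreed to within about 0.01. Over the settings examined, random loss stays within about 0.05 to 0.09. One worst performer lost gives about 0.05 to 0.07.

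**5. If terminated patients were left out instead of filled in.** Removing the lowest two or three from one arm gives a shift of 0.15 or 0.21 SD and type I error of 0.08 or 0.11. The bias therefore does not come only from the imputation rule, although that rule can enlarge it.

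**The case against.** The best-interest condition is an ordinary participant-protection clause and is not itself an error. Each investigator's right is confined to their own part of the study, and reasons are recorded. The Statistics section lists patients who do not receive study therapy separately from those lost to outcome assessment, so the authors know the distinction. A condensed article may also leave post-discontinuation data collection to the full protocol.

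Much of this stands. It does not remove the point, because the article states the rule and does not merely omit detail. What may be terminated is participation. The restriction to one part of the study governs when the right can be used, not what it ends. The distinction in Statistics is not carried into the clause that decides whether a patient is measured.

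A reader might infer that variable ventilation will lose more patients because only that arm depends on computer control. The document does not support this. The Intervention section handles a malfunction by switching back to conventional ventilation, and other ventilatory or medical problems by the anesthesiologist's discretion with documentation. Neither is described as ending participation. The direction of any imbalance is therefore unknown.

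Arm-aware termination also concerns mainly the intraoperative investigator, since the postoperative one is blinded to treatment.

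**Conclusion.** The clause can produce arm-dependent missing day-1 FVC, and neither the intention-to-treat statement nor last observation carried forward repairs that. It would go too far to say that it will. The document gives no termination rate, and the foreseeable intraoperative problems have routes that do not end participation.

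The size depends on informative loss. Two or three worst performers lost from one arm would shift the comparison by about 0.1 to 0.3 or 0.15 to 0.45 SD in that arm's favour, against a planned effect of 1.086 SD. Type I error would be about 0.07 to 0.13 or 0.10 to 0.23. Random losses do much less, and a single loss matters little. These ranges rest on the assumed fall, correlation and number lost. If FVC did not fall at all by day 1, the formula above gives at most 0.08 × 0.5 × 1.74 = 0.07 SD for two patients lost.

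The effect should not be expressed in litres, because the document gives only a standardised effect and no SD. The change is worth making: the exposure is on the primary endpoint and the correction is a matter of wording.

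**What to change.** Amend Study dropouts so that:

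- an investigator's decision ends the assigned ventilation, or a particular study procedure judged to be against the participant's interest;
- the patient otherwise stays in the trial in the randomised arm, and day-1 FVC and the later visits are still collected where feasible, unless the patient withdraws consent;
- the reason, the time and the role of the person who decided are recorded, and counts are reported by arm.

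The clinical criteria for stopping remain with the investigators, and freedom to change care is untouched. The cost is a short protocol clarification and a few extra day-1 and later assessments in patients who would otherwise have been dropped. The wording cannot recover FVC from patients who withdraw consent or cannot perform spirometry, so some missing data will remain to be handled in the analysis.

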### Statistics

Sample size calculation was based on a previous study using FVC as a measure of postoperative pulmonary function following general anesthesia [3]. In the present study, effect size was estimated as 1.086, alpha was defined as 0.05 and power as 0.95. Using a two-tailed Mann–Whitney-*U*-test, sample size calculation yielded 25 patients per group. Analysis was performed using GPower (Software Version 3.1.3, University of Düsseldorf, Germany).

Exploratory analysis will include mean and standard deviation for normally distributed variables. Non-normally distributed variables will be expressed by their medians and interquartile ranges. Categorical variables will be expressed as n (%). Parametrical or non-parametrical tests will be used as appropriate to analyze the data. *P* values for multiple comparisons will be adjusted according to the Bonferroni procedure.

In case of loss to follow-up or consent withdrawal from the trial, the causes will be reported. ITT and per protocol (PP) analysis will be conducted. For the intention-to-treat analysis, data will be processed for all trial patients in the groups in which they were randomized. The PP analysis will be performed as a secondary analysis if there are a considerable number of patients who do not receive study therapy or are lost to outcome assessment. Missing data will be handled by means of the last observation carried forward method.

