### Screening, enrollment, randomization and blinding

Investigators screen consecutive patients planned for open abdominal surgery with an expected duration >3 h at the University Hospital Dresden, Germany during regular anesthesiological preoperative evaluations. The screening started in September 2012, and a recruitment time of 24 months has been defined based on the incidence of major abdominal surgery and patient characteristics at our hospital. Demographic data of screened patients are recorded regardless of whether they meet the enrollment criteria. Informed consent is obtained from all patients prior to surgery. All screened patients are reviewed with respect to inclusion and exclusion criteria as summarized in Table 1.

**Table 1 T1:** Inclusion and exclusion criteria for the PROVAR trial

**Inclusion**	**Exclusion**
Patients scheduled for elective open abdominal surgery with expected duration >3 h	Chronic lung disease, except COPD GOLD stage I and II and untreated bronchial asthma
ASA class 2 and 3	Body mass index >40
Expected extubation in the OR	Hypersensitivity or allergy against one of the drugs administered during the study or against drugs with similar chemical structure
Informed consent to participate in the study signed by the patient	Participation of the patient in another clinical trial within the last 4 weeks
	History of substance abuse or any other mental status possibly affecting informed consent
	Pregnancy or breastfeeding
	Women in an age range of possible pregnancy if not:
	• Postmenopausal (12 months of amenorrhea or 6 months of amenorrheawith serum FSH >40 lU/ml)
	• Postoperative (6 weeks after bilateral ovariectomy with or without hysterectomy)
	• Regular and correct use of contraceptives with failure rate of <1% per year
	• Sexual inactivity
	• Vasectomy of sexual partner
	Suspected low patient compliance
	Contraindication for MRI exams
	Mechanical ventilation within the last 30 days

ASA, American Society of Anesthesiologists; OR, operating room; COPD, chronic obstructive pulmonary disease; GOLD, global initiative for chronic obstructive lung disease; FSH, follicle-stimulating hormone; MRI, magnetic resonance imaging.

Randomization is performed by random block randomization with fixed 1:1 randomization ratios within blocks of 2 × 10, 3 × 6 and 3 × 4 patients using closed envelopes.

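### The article fixes single-step Bonferroni for multiple comparisons; Holm gives the same familywise error control and is never less powerful

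*Protocol article*

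**What the plan says.** The Objectives and design section names a single primary outcome: "Primary endpoint is the FVC on the first postoperative day". The list that follows begins "Secondary endpoints are plasma concentrations of interleukin (IL)-6, IL-8 and tumor necrosis factor alpha (TNF-α" and goes on to capillary PcO2, peak expiratory flow, FEV1, intraoperative PaO2/FIO2, the distribution of ventilation by impedance tomography, atelectasis on MRI, and pulmonary complications by the modified clinical pulmonary infection score. That makes ten secondary endpoints with the three cytokines counted separately, or eight with them counted as one.

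The Statistics section sizes the trial on the primary alone: "effect size was estimated as 1.086", "alpha was defined as 0.05 and power as 0.95". It continues: "Using a two-tailed Mann–Whitney-*U*-test", "sample size calculation yielded 25 patients per group". Alpha is not divided. In the next paragraph, after the sentences on descriptive summaries and choice of test, comes the only multiplicity rule in the article: P "values for multiple comparisons will be adjusted according to the Bonferroni procedure". The article does not say which comparisons form the family or how many there are, and it does not mention the primary endpoint in this connection.

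**The concern.** Part of the trial's hypothesis is tested only through secondary endpoints. Reduced systemic inflammation rests on the cytokines, and redistribution of ventilation rests on impedance tomography. With 25 patients per group and ten secondary comparisons, single-step Bonferroni tests each at 0.05/10 = 0.005. A true but moderate effect can easily miss that threshold.

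Holm compares the smallest P value with 0.05/10, the next with 0.05/9, and so on, stopping at the first failure. It needs no further assumption and holds the same familywise error rate. Where several secondary effects are real, Bonferroni gives up power that this error rate would have allowed.

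**Working it through.** **1. The plan's own figure.** Inputs from the Statistics section: d = 1.086, two-sided alpha 0.05, power 0.95, Mann–Whitney test. Allocation is 1:1 ("fixed 1:1 randomization ratios within blocks"). Method: noncentral t power, with n per group multiplied by the Mann–Whitney asymptotic relative efficiency for normal data, 3/π = 0.955.

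- Effective n per group = 25 × 0.955 = 23.87; df = 2 × 23.87 − 2 = 45.7.
- Noncentrality = 1.086 × √(23.87/2) = 1.086 × 3.455 = 3.752.
- Power at 25 per group = 0.957; at 24 per group = 0.949.

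The stated 25 per group is reproduced at the full 0.05. The sizing therefore treats the primary endpoint as one unadjusted test.

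**2. Bonferroni power per secondary endpoint.** Ten comparisons give alpha 0.005 each, so the two-sided critical value is z = 2.807. With the normal approximation and the same efficiency factor, power ≈ Φ(3.455 × d − 2.807).

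- d = 0.8: Φ(2.764 − 2.807) = Φ(−0.043) = 0.48.
- d = 1.086: Φ(3.752 − 2.807) = Φ(0.945) = 0.83.

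**3. Holm against Bonferroni.** Simulated correlated z-values for ten endpoints at 25 per group. The correlation of 0.4 and the effect sizes are assumptions; the article gives none for the secondary endpoints. The figures are average power per true effect.

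| True effects | Bonferroni | Holm | Gain |
|---|---|---|---|
| 2 of 10 at 0.8 SD | 0.48 | 0.49 | 0.01 |
| 5 of 10 at 0.8 SD | 0.48 | 0.51 | 0.03 |
| 10 of 10 at 0.8 SD | 0.48 | 0.59 | 0.11 |
| 10 of 10 at 1.086 SD | 0.83 | 0.92 | 0.09 |

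At correlations of 0 and 0.7 the first three gains barely change, and the last lies between about 0.08 and 0.12. The gain cannot be negative, because every Holm threshold is at least as large as the Bonferroni threshold.

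**4. The primary endpoint, if it were in the family.** The formula of step 1 at alpha 0.05/k and 25 per group gives:

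- k = 4 (the four postoperative FVC measurements: days 1, 3, 5 and before discharge): 0.87.
- k = 9 (primary plus eight secondaries): 0.79.
- k = 11 (primary plus ten secondaries): 0.77.

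The article states none of these families, so the figures show only what a clarifying clause would guard against.

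**5. Overall error if the primary stands outside.** With the primary at 0.05 and the secondary family at 0.05 without a gate, the chance of at least one false rejection is 1 − 0.95² = 0.0975 if the two are independent, and at most 0.05 + 0.05 = 0.10.

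**The case against.** Bonferroni is valid and familiar, and it has simple matching simultaneous confidence intervals, which Holm lacks. Choosing between the two is a matter of efficiency. The larger gains need most or all secondary endpoints to have sizeable effects, and with two true effects the gain is about one percentage point. One of the ten, pulmonary complications, is an event-type outcome to which a shift in SD units does not naturally apply. The definition of the family is commonly left to the analysis plan or full protocol, neither of which is shown. All of this stands. It limits the size of the point but does not remove it, because the article itself commits to the procedure and another one is at least as powerful for the same error rate.

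A reader might go further and infer that the Bonferroni rule also covers the primary endpoint, so that the planned 95% power falls to 0.77. The text does not support that. The rule applies to multiple comparisons, and FVC at one time point in two arms is a single comparison. The sample size reproduces at an undivided 0.05. That the rule does not expressly exempt the primary endpoint is missing detail, not a contradiction.

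**Conclusion.** The point holds as a minor matter of efficiency. The article fixes a valid multiplicity procedure where another, with the same error control under the same assumptions, is never less powerful. Across the 0.8 SD scenarios the gain in average power per true effect runs from about 0.01 to about 0.11, given ten secondary endpoints, 25 per group, an assumed correlation of 0.4 and assumed effects. If the family is smaller or few effects are real, the gain is towards the low end. No loss of power for the primary endpoint is demonstrated; on the natural reading it keeps its planned power of about 0.957.

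**What to change.** Replace the Bonferroni sentence in the Statistics section with wording such as:

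> *FVC on the first postoperative day is tested once at two-sided 0.05, outside the family of secondary comparisons. P values for the secondary comparisons are adjusted by the Holm procedure at a familywise level of 0.05.*

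If the sponsor wants 0.05 to hold over the primary and secondary endpoints together, add that the secondary comparisons are tested only if the primary is significant. Without that gate the overall rate can approach 0.10.

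The cost is one sentence, with no change to sample size or data collection. The drawback is that Holm has no simple matching simultaneous confidence intervals, so intervals for secondary endpoints would be reported unadjusted and labelled as such.

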## Background

General anesthesia promotes pulmonary atelectasis [1] and this effect is further enhanced during open abdominal surgery [2], mainly due to the use of muscle paralysis. Indeed, with relaxation of the diaphragm, the intra-abdominal pressure is transmitted to the intrathoracic cavity, promoting compression of the lung parenchyma and resulting in more atelectasis. Atelectasis and the decrease in pulmonary gas volume can persist during the postoperative period. It has been shown that forced vital capacity (FVC) and other variables of lung function are reduced for up to three hours postoperatively compared to pre-operative values [3]. It has been shown that noninfectious pulmonary complications like atelectasis or pleural effusions may favor the development of pneumonia [4], and increased bacterial translocation has been found from atelectatic lung regions [5]. The presence of atelectasis may promote the development of ventilator-associated lung injury due to cyclic collapse and re-opening of atelectatic lung regions [6]. Consequently, atelectasis formation is associated with increased length of stay in the recovery room and also with increased admission to the intensive care unit [7,8].

The application of positive end-expiratory airway pressure (PEEP) combined with lung recruitment maneuvers has been shown to reduce atelectasis and improve lung function [9,10]. However, recruitment maneuvers and high levels of PEEP carry the risk of barotrauma and deterioration of hemodynamics, and do not represent standard of practice in general anesthesia.

Recent data suggest that variable ventilation may improve lung function without causing structural damage to the lungs or increasing pulmonary inflammatory response in the experimental [11] and clinical setting [12]. One important mode of action of variable ventilation is the recruitment of previously collapsed lung areas. Variable ventilation is not only able to induce lung recruitment [13], but also to keep alveoli open once they are recruited [14]. This mechanism is of special importance in the presence of low or moderate settings of positive end-expiratory pressure, as planned in the presented trial. Variable ventilation mimics some aspects of the physiological ventilation pattern of healthy, spontaneously breathing individuals, but so far it is not known if variable ventilation is able to improve postoperative pulmonary function and reduce systemic pro-inflammatory response after surgery.

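### Last observation carried forward replaces any missing day-1 FVC, the primary outcome, with the patient's pre-surgery value

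*Protocol article*

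**What the plan says.** - **Missing data** (Statistics): "Missing data will be handled by means of the last observation carried forward method". The sentence is unqualified and no other missing-data method is named.
- **Primary endpoint** (Objectives and design): "Primary endpoint is the FVC on the first postoperative day".
- **Visit 1, before surgery** (Time course of interventions/study protocol): "informed consent is obtained, demographic data are recorded and spirometry, EIT measurements and capillary blood gas analysis performed to retrieve baseline data".
- **Visit 2, during surgery** (same section): "hemodynamics, as well as spirometric data, are recorded from the monitoring system and the ventilator, respectively".
- **Visit 3** (same section): "Visit 3 takes place on the first postoperative day. Spirometry, lung MRI, EIT, plasma blood sampling and capillary gasometry are performed". Spirometry is repeated on postoperative days 3 and 5 and before discharge.
- **Analysis sets** (Statistics): the intention-to-treat analysis takes all trial patients as randomised. A per-protocol analysis is secondary and is run only if a considerable number go untreated or are lost to outcome assessment. Causes of loss to follow-up or consent withdrawal are to be reported.
- **Background**: citing an earlier study, FVC is said to be below its preoperative level for up to three hours after surgery. Reduced gas volume is said to be able to persist postoperatively.

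**The concern.** Carrying the last value forward is defensible only if the earlier value is a plausible stand-in for the missing one. Here the earlier value was measured before the event whose effect the trial studies. Filling it in assumes no postoperative decline, while the trial's rationale is that such a decline occurs and that ventilation mode can lessen it.

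Two things are at stake. If similar numbers are missing in both arms, the imputed values carry no treatment effect, so the estimated difference shrinks and power falls. If the numbers differ, the arm with more missing patients receives more pre-surgery values and its FVC is raised artificially. Missing day-1 values are foreseeable: the Study dropouts section allows withdrawal by the patient and termination by either investigator. The planned 50 patients equal 2 × 25, so there is no allowance for loss.

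**Working it through.** **1. Which value is carried forward.**

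| Visit | FVC available? |
|---|---|
| 1, preoperative | Yes (baseline spirometry) |
| 2, surgery | No: ventilator readings in anaesthetised patients under neuromuscular blockade, without a forced manoeuvre |
| 3, postoperative day 1 | Primary endpoint |

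The last observation before visit 3 is visit 1. For any patient with a missing day-1 value, the imputed change is baseline − baseline = 0. This step needs no assumption.

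**2. The plan's own figure.** Inputs from Statistics: effect size 1.086, two-sided alpha 0.05, power 0.95, Mann–Whitney test. I used the noncentral t with the rank test's efficiency of 3/π = 0.955 for normal data. At 25 per group the effective n is 25 × 0.955 = 23.9 and the noncentrality is 1.086 × √(23.9/2) ≈ 3.75. Power is 0.957, and 25 is the smallest n that reaches 0.95. The stated sample size reproduces.

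**3. Expected difference, values missing at random.** Assumptions, none of them in the article: preoperative FVC 3.8 L (SD 0.9); day-1 SD 0.7 L; mean day-1/preoperative ratio r of 0.5–0.7 without treatment effect; correlation 0.7. The true difference is then 1.086 × 0.7 = 0.76 L.

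- *Equal missing share m.* Baselines are the same on average in both arms, so the expected difference is 0.76 × (1 − m). With 3 of 25 per arm: 0.76 × 0.88 = 0.67 L.
- *Four conventional and one variable missing.* The expected difference is 0.76 × 24/25 − (3/25) × 3.8 × (1 − r) = 0.73 − 0.456 × (1 − r). That is 0.50 L at r = 0.5 and 0.59 L at r = 0.7.

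**4. Power by simulation** (25 per arm, two-sided Mann–Whitney at 0.05, values missing at random).

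- None missing: about 0.95.
- 1 per arm: 0.93–0.94.
- 3 per arm: about 0.86, against 0.92–0.94 for complete cases.
- 5 per arm: 0.72–0.77.

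For 10% missing, dilution alone would give d = 1.086 × 0.90 = 0.98 and power 0.91. The simulated loss at 12% (3 of 25) is larger because the imputed values also widen the spread.

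**5. Type I error by simulation** (no true effect; the lowest four conventional-arm and lowest one variable-arm values missing).

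| Handling | Type I error |
|---|---|
| Carry forward, ratio 0.5–0.7 | 0.16–0.21 |
| Carry forward, ratio 0.8–0.9 | 0.08–0.11 |
| Complete cases | 0.11–0.14 |
| Worst rank | at or below 0.05 |

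Under carry-forward almost all false positives favour the arm with more missing patients.

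**6. A second missingness model.** Here the fall is 1.5–2.5 SD, low values are more likely to be missing, and the split is 5 v 2. Type I error is 0.16–0.20 with carry-forward, 0.11–0.13 with complete cases and 0.02–0.03 with worst rank. With the true effect of 1.086 SD and five conventional and two variable values missing, carry-forward estimates 0.67–0.79 SD with power 0.67–0.82.

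**The case against.** The strongest reply is that the harm depends on facts the article does not give. Patients are elective, ASA 2–3 and expected to be extubated in the operating room, and the endpoint is one day away, so few values may be missing. With one missing per arm the power loss is negligible. With the lowest 2 v 1 missing and no effect, type I error is 0.08–0.09, against about 0.08 for complete cases. This stands as a limit on size. It does not justify a rule whose imputed value is wrong whenever it is used.

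The Background figure covers up to three hours and gives no day-1 fall. That also stands, although choosing day 1 as the primary time point presupposes that a deficit is still present then. Shifting all day-1 values by a constant leaves complete-case ranks unchanged, so the complete-case 0.11–0.14 holds for any ratio. At a ratio of 0.8–0.9, carry-forward is therefore no worse than complete cases in the null scenario.

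A reader might infer more than the documents support:

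- *That the missing patients are the sickest.* The article does not say why spirometry would be missing. Inability through illness is the most damaging plausible reason, but not a documented one.
- *That such patients get nearly the best score.* In the step 5 scenario, imputed values average about the 57th to 82nd percentile of day-1 FVC, because low day-1 values go with low baselines.
- *That a harmful mode would look protective.* Only no effect and a true benefit were simulated.
- *That the whole type I inflation comes from the rule.* Much of it comes from the assumed outcome-related missingness. When unequal numbers are missing at random, type I error is only 0.05–0.07.

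The per-protocol analysis and the reporting of causes help a reader judge the result. Being conditional and secondary, the per-protocol analysis does not repair the primary one. Nor can the point be left to an analysis plan that is not shown, because the article itself fixes the method.

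**Conclusion.** The point holds as a defect in a stated rule. That a missing primary outcome becomes the pre-surgery value follows from the visit schedule alone, and it conflicts with the trial's own rationale.

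The size is illustrative. It rests on assumed missing numbers, an assumed day-1 fall and an assumed correlation of 0.7. With balanced random missingness the cost is dilution and lost power: small at one per arm, material at three. With unequal, outcome-related missingness and a fall of 30–50%, the false-positive rate is three to four times nominal (0.16/0.05 ≈ 3; 0.21/0.05 ≈ 4), and above that of complete cases. The sample size calculation is not at fault. The change should be made before unblinding, because a missing-data rule chosen afterwards would not be credible.

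**What to change.** 1. Delete last observation carried forward for the primary endpoint, and state that a preoperative value is never carried into a postoperative visit.
2. Keep the Mann–Whitney comparison on which the sample size rests. Give the worst rank to patients who could not perform day-1 spirometry because of death, continued ventilation or a pulmonary complication.
3. Handle other missing day-1 values by multiple imputation from baseline FVC and the FVC already scheduled at later visits. A repeated-measures model can serve as a sensitivity analysis. Both assume missingness at random, so neither replaces the worst-rank rule where the reason is clinical.
4. Apply the ban in item 1 to secondary endpoints that have a preoperative measurement, notably FEV1, peak expiratory flow, capillary oxygen pressure and MRI atelectasis on day 1. No size was calculated for these.

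Cost: one paragraph, somewhat more analysis work, and a classification of the reason for each missing day-1 test made while blinded to arm. No new data or patients are needed. Worst rank also has a price: in the second model, with a true benefit and two conventional and five variable values missing, its power was about 0.77. It should therefore be confined to the named clinical reasons.
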